## 2 INTRODUCTION

Migraine is a common disorder with a prevalence of 12 % in the general population, and is more frequent in women (18%) than in men (6%). Symptom frequency, severity, and impact on patients' quality of life varies.

A treatment plan should consider not only the patient's diagnosis, symptoms, and co-existent or comorbid conditions, but also the patient's expectations, needs, and goals. In order to improve the quality of life, prevent permanent disability and chronicity, preventive therapy (prophylaxis) is often necessary. Prophylactic migraine therapy includes drug and non-pharmacological treatments and a reduction of monthly migraine days can be achieved. A common problem of drug therapy are insufficient effects and/or intolerable side effects. Non-pharmacological therapies include regular aerobic endurance sports, relaxation techniques and cognitive-behavioral therapy (CBT) methods used in psychological pain therapy (pain management, trigger identification and coping). Access to on-site psychological therapy, especially CBT, is limited by the number of psychotherapists specialising in pain disorders, both in urban and even more so in rural areas.

Digital health applications (or apps) allow scalability, efficiency, and behavior change. Michie et al. defined the smallest, observable, replicable intervention components with the potential to bring change in behavior as behavior change techniques (BCTs). BCTs could also be "a systematic procedure included as an active component of an intervention designed to change behavior". For example, app features and functions can be designed based on different BCTs to improve user engagement: "prompts/cues" could be implemented as an app notification to remind users to fill in questionnaires and "feedback on behavior" could potentially maintain the user's motivation by providing instant feedback. Besides, "goal-setting" and "self-monitoring" are also commonly implemented BCTs in smartphone apps. Digital health applications for headache care can offer new options such as an electronic headache diary which offer more features than the established paper-pencil based headache diaries, e.g. by automatic analysis of potential trigger factors or headache attack classification. In addition to a documentation function in the form of a headache and medication intake diary, apps can also contribute to a better understanding of the headache disorder through education and provide electronically based guidance for non-pharmacological interventions, such as evidence-based CBT exercises. This app data can provide healthcare professionals with information relevant for optimised and effective treatment. However, the current commercially available headache apps have not been evaluated for effectiveness, or their content is not evidence-based.

Since 2020, digital medical devices can be prescribed to patients by physicians and psychotherapists within the framework of the DiGA – Digital Healthcare Act (Digitale-Versorgung-Gesetz) in Germany. Digital medical devices such as smartphone-based programmes can thus be made reimbursable by statutory health insurances, and hence made broadly available to the public. Since many

smartphone-based therapies have yet to be evaluated for effectiveness, the DiGA provides the framework to gather this evidence within 12 months.

The smartphone app M-sense Migräne ([www.m-sense.de](http://www.m-sense.de)) aims to enable migraine patients to track headache attacks, symptoms, medication intake and trigger factors, as well as to have access to evidence-based and evidence-informed treatment options within a digital environment. Due to the individual data collected by the e-diary (electronical diary), education on disease- and trigger management, relaxation exercises and instructions for endurance sports can automatically be tailored to the app user and his/her specific needs. However, to be reimbursed by statutory health insurance companies in Germany the app's effectiveness has to be shown in a study. To achieve this aim a post-market clinical investigation according to Digitale-Versorgung-Gesetz (DVG) will be prepared.

### 3 OBJECTIVES

The aim of this study is to evaluate the effectiveness of the M-sense Migräne app in reducing migraine days in migraine patients (ICD-10 G43 = episodic and chronic migraine) compared to patients in a waiting list group who have no access to the app intervention.

As secondary objectives the study evaluates headache days, migraine-specific quality of life, disability/headache attributed lost time, migraine-specific health literacy, and headache management self-efficacy. Of further interest are the evaluation of safety, adherence, and drug consumption for acute treatment, concomitant non-pharmacological interventions.

## 4 INVESTIGATION AND PROCEDURES

### 4.1 Overall study design

This is a two-armed, open-label, parallel-group, randomized, controlled trial. Potential study participants will be invited to participate in a 28-days baseline phase in which data on headache days and migraine attacks will be collected. This data will be used for the eligibility check. Furthermore, a physician (via video consultation) will inform about the study, validate the patient-reported migraine diagnoses and obtain the informed consent from study participants. After final informed consent and verification of the patient's eligibility for the study in the video consultation, patients will be randomly allocated to one of the two groups in a 1:1 ratio to gain access either to the full M-sense Migräne app or the control study app with only data input features (only as a diary visible for one week without attack classification with daily headache question and questionnaires, no app interventions and no feedback on data or behavior). The primary outcome will be the migraine days per month (defined as 28 days in weeks 9 to 12).

The DiGA-study will be completed after 12 weeks follow-up per study participant.

Additional data will be collected afterwards. Then both groups receive the full M-sense Migräne app and use the intervention for 12 weeks (see Figure 1). This will allow to gather data over 24 weeks in the intervention group and increase the motivation in the control group to participate in the study and to provide data over 12 weeks without access to the intervention.

[figure not shown]

Figure 1. Study flow and design of RCT

### 4.2 Justification of study design and approach

The study takes into account the current guidelines of the International Headache Society for controlled trials on preventive pharmacological treatment of episodic migraine and preventive treatment of chronic migraine in adults. We decided to perform a randomized controlled trial to reduce the confounding of results as much as possible. Because of the type of intervention used within the study

blinding of participants is not possible. Nevertheless, the physician classifying the headache attacks and the statistician performing the analysis will be blinded for the group allocation of the patients. To assure high relevance of the study results to patients, a patient reported outcome (PRO) was used as primary endpoint. We decided to document all outcomes within the app in both groups to reduce the bias that different types of documentation in intervention and control group might introduce to the data.

Although we assess most of the relevant diagnostic criteria within the app we decided to have the verification of the diagnoses by a physician. To stay within the digital framework of the study approach and taking into account possible restrictions because of the new corona virus SARS-CoV-2 this is planned as video consultation.

The DiGA study is planned for 12 weeks per patient (until primary endpoint), to gather further data and to allow the control group to receive the M-sense Migräne app after 12 weeks, a 12 week follow-up study will be added to the DiGA study.

## 5 PARTICIPANTS AND GROUP ALLOCATION

### 5.1 Recruitment

The study will be announced to possible participants and health professionals using different media channels. Additionally, participants can be recruited by self-referral via the German Apple App store (Apple Inc.) and Google Play Store. The recruitment of 346 patients within 6 months seems feasible, because in the last app study by the study group around 350 participants were recruited within 10 months only through the German Apple App store without applying other recruitment approaches. Additionally, this study will also recruit Android users. To support faster recruitment a fee of 80 Euro will be provided to study participants for a 12-week documentation within the app.

### 5.2 Inclusion and exclusion criteria

For inclusion in the study the patients have to fulfill the following **inclusion criteria**:

- Adults  $\geq 18$  years with migraine (ICD-10 G43) diagnosed by a physician
- Disease duration of at least 1 year (patient reported)
- At least 3 migraine days in the previous 4 weeks (baseline)
- Disease onset before age 50 y
- Migraine screening questions positively answered
- Smartphone ownership and smartphone literacy
- Sufficient knowledge of German

- Informed consent

Patients will be excluded from the study if they fulfill any of the following **exclusion criteria**:

- Planned pregnancy, pregnant and breastfeeding women (due to associations between hormone status and headache and migraine days)
- Medication overuse headache (assessed by physician question, app data during baseline > 15 days with medication)
- Headache app / M-sense or similar app use of at least a month during the last 12 months
- Planned start of a new treatment for migraine within the next 4 months
- Simultaneous participation in another interventional study
- Users who have filled in the diary <3 days/week during baseline

Inclusion and exclusion criteria will be assessed by a physician via video consultation, and within the app before final study entry after the 28 days baseline phase.

### 5.3 Verification of diagnosis

The diagnosis will be verified by a physician via a video consultation and will also be checked by in-app questions before randomization.

### 5.4 Assignment to study groups

We will use a server-based randomization table implemented in the app and created by a statistician using the RANUNI random number generator of the SAS/STAT version 9.2 (SAS Inc). Study participants fulfilling the eligibility criteria who have provided informed consent will be randomized in a 1:1 ratio by block randomization with a fixed block length to one of two groups (M-sense Migräne app or control group with control app). Randomization will be stratified for the type of migraine (episodic or chronic). To assure allocation concealment the randomization list will not be accessible by the user or the study staff involved in possible communication with the participants.

### 5.5 Withdrawal of study participants from treatment or assessment

Study participants have the right to abort the study at any time and without providing a reason. They can decide if they a) do not want to participate in the upcoming interventions and still want to complete questionnaires or b) do not want to participate in the upcoming interventions and do not want to complete

upcoming questionnaires or c) if they are withdrawing their informed consent and all previous information should be deleted. We will assess reasons for withdrawal.

In case of safety concerns, the patient will find information in the app on how to contact the study office where these aspects can be discussed. If general safety concerns arise, the study will be stopped and participants informed via the app and by the contact information they had provided.

## 6 OUTCOMES

### 6.1 Summary of assessments

Table 1 provides an overview about the assessments and the time points. The data is documented with the app.

**Table 1. Outcome and other assessments and time points, \*documented by physician, #in app user data**

| Time (week)                               | Baseline
4 weeks | before
randomization | Diary
12 weeks DIGA
+ 12 weeks after | 4     | 8 | 12 | 24-
weeks
for
follow-
up study |
|-------------------------------------------|---------------------|-------------------------|--------------------------------------------|-------|---|----|--------------------------------------------|
|                                           |                     |                         |                                            | weeks |   |    |                                            |
| Eligibility criteria                      | x                   | x*                      |                                            |       |   |    |                                            |
| Migraine or chronic
migraine diagnosis | x                   | x*                      |                                            |       |   |    |                                            |
| Participant characteristics               | x                   | x*                      |                                            |       |   |    |                                            |
| Migraine days                             | x                   |                         | x                                          |       |   |    |                                            |
| Headache days                             | x                   |                         | x                                          |       |   |    |                                            |
| Moderate/severe
headache days          | x                   |                         | x                                          |       |   |    |                                            |
| HIT-6                                     |                     | x                       |                                            |       |   | x  | x                                          |
| HMSE-G-SF                                 |                     | x                       |                                            |       |   | x  | x                                          |
| HALT-30                                   |                     | x                       |                                            |       |   | x  | x                                          |
| Migraine specific health
literacy      |                     | x                       |                                            |       |   | x  |                                            |
| Medication use                            | x                   |                         | x                                          |       |   |    |                                            |
| Use of app interventions                  |                     |                         | x #                             |       |   |    | x #                             |
| Safety measures                           |                     |                         |                                            | x     | x | x  | x                                          |

### 6.2 Primary outcome

The primary outcome are the **migraine days per month** (defined as 28 days) after 12 weeks (week 9 to 12). Migraine days will be based on the information in the headache diary. Headache attacks will be classified according to ICHD-3 (criteria B to D) by a physician blinded for the patient's group allocation (see SAP 2.1 for further description). A migraine day is defined as a calendar day on which a single or multiple migraine attacks have been reported.

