**Figure 2. Screenshots of the study app**

a) The comprehensive **headache diary** allows a real time tracking of headache occurrences, including headache characteristics, attendant symptoms and experienced pain intensity levels. These headache entries are automatically classified by the M-sense headache classification algorithm, a digitalized version of the ICHD-3-based headache classification. The algorithm allocates single headache attacks to the phenotypes migraine, tension-type headache (TTH), and unclassified headaches. The validity of M-sense's algorithm was assessed by comparing the classification of single headache attacks performed by the algorithm to the attack classification performed by a certified neurologist specialised in headache medicine. The substantial level of agreement between the neurologist and the algorithm was obtained (unweighted kappa=0.74). Most cases of disagreement were due to inadvertent mistakes of the neurologist as identified in the disagreement validity assessment.

b) The **diary for medication intake** allows users to track intake of their prophylactic and acute pain medication and to receive information on proper intake of medications and the potential hazards of medication overuse.

- c) The **diary for trigger factors** list potential migraine trigger factors, e.g. sleep duration, period, alcohol consumption, stress (for details see Wöber & Wöber-Bingöl, 2011). Through descriptive statistics potential individual triggers can be detected.
- d) The **analysis function and physician report** analyses and visualizes the data entered into the app, including headache types, monthly headache occurrence, monthly average pain intensity and frequency of headaches, trigger statistics, headache distribution by time-of-day, day-of-week, and days-in-month and medication intake in weekly and monthly reports, as well as via the in-app calendar. This helps users to self-monitor the course of the disease and their medication intake. The report can be used to facilitate patient-physician communication.
- e) For the **personalized education about disease- and trigger management** the M-sense Migräne app includes 20 individualized knowledge lessons about migraine (e.g. symptoms, trigger factors and causes) and its treatment options (acute and preventive).

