## 6.1 PRIMARY OUTCOME

The primary outcome are the **migraine days per month** (defined as 28 days) after 12 weeks (week 9 to 12). Migraine days will be based on the information in the headache diary. Headache attacks will be classified according to ICHD-3 (criteria B to D) by a physician blinded for the patient's group allocation. A migraine day is defined as a calendar day on which a single or multiple migraine attacks have been reported.

The information necessary for the classification as migraine attack ICHD-3 criteria B to D (see below) will be used based on data of the diary.

The criteria B to D are:

- B. Headache attacks lasting 4-72 hr (untreated or unsuccessfully treated)
- C. Headache has at least two of the following four characteristics:
  - 1. unilateral location
  - 2. pulsating quality
  - 3. moderate or severe pain intensity
  - 4. aggravation by or causing avoidance of routine physical activity (eg, walking or climbing stairs)
- D. During headache at least one of the following:
  - 1. nausea and/or vomiting
  - 2. photophobia and phonophobia

The physician will manually classify the headache attacks based on the raw data of the diary according to ICHD-3 (criteria B to D). Any information which has to be manually added to the analysis dataset will be based on double entry and subsequent comparison to control for data entry errors. In a next step we will compare the results from the manual classification with the M-sense algorithm^3. In case of discrepancies the physician will re-evaluate his/her classification and make a final decision.

The number of migraine days per month is obtained by adding up the number of migraine days within four consecutive weeks (28 days). When the respective information needed for the classification has been sufficiently documented by the patient the headache days will be classified into three categories: 1. migraine days, 2. days with tension type headache, or 3. other headaches (do not meet criteria for migraine days or days with tension type headache). If the respective information provided by the patient is not sufficient for classification, the classification value for this day would be seen as a missing value.

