### 10.4.3 Missing Data

Data completeness in the diary will be considered on a weekly basis and data are defined as missing if the daily headache question has not been answered at least 3 days per week during a respective week. Missing data for the diary will be imputed on the week-level. Missing data in questionnaires, will be imputed based on the measurement time point. For missing data imputation a multiple imputation procedure will be used (regression based multiple imputation method stratified by treatment group and type of disease (chronic or episodic migraine) with five imputed datasets.

Imputation model: imputations for continuous data will be generated with the predictive mean matching method (pmm). The following variables will be used as predictors in the imputation process for missing values at later time points: headache days, migraine days, age, gender, education level, duration of migraine disease, quality of life (HIT-6), self-efficacy (HMSE-G-SF), headache attributed burden (HALT-30), and migraine-specific health literacy.

In case the respective information for the classification of the headache days into migraine days, days with tension type headaches and other headaches has not been documented, we will use a conservative approach and assume a migraine day. Therefore, we will replace these missing values with migraine days in both groups, for the intervention phase as well as for the baseline phase.

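### As worded, the SAP's replacement rule can score as migraine days headaches whose documented fields already exclude migraine, because it is triggered by the three-way classification and not by migraine yes/no

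*Combined protocol and SAP*

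**What the plan says.** Protocol (evaluation concept) 6.2, repeated in 11.6 and in SAP 6.1, defines the unit of the endpoint: "A migraine day is defined as a calendar day on which a single or multiple migraine attacks have been reported". Attacks are judged by a blinded physician on ICHD-3 criteria B to D, and migraine days are summed over 28 days. Tension-type and other headache days do not enter that sum.

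SAP 6.1 nevertheless sets up a finer classification. Where the patient has documented enough, "the headache days will be classified into three categories: 1. migraine days, 2. days with tension type headache, or 3. other headaches", the last being headaches that "do not meet criteria for migraine days or days with tension type headache". Where the patient's information "is not sufficient for classification, the classification value for this day would be seen as a missing value". The SAP lists criteria B to D for migraine. It gives no criteria for tension-type headache and does not define sufficient documentation.

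SAP 10.4.3 then deals with the missing values. When the information for "the classification of the headache days into migraine days, days with tension type headaches and other headaches has not been documented", the day is assumed to be a migraine day, in both groups, at baseline and during the intervention phase.

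SAP 6.1 also plans a check: "In a next step we will compare the results from the manual classification with the M-sense algorithm", with discrepancies going back to the physician for a final decision. Protocol 7.1 describes the algorithm's output: "The algorithm allocates single headache attacks to the phenotypes migraine, tension-type headache (TTH), and unclassified headaches".

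**The concern.** The endpoint and the replacement rule ask different questions. The endpoint asks whether B, C and D are all met. The rule asks whether the day can be placed in one of three categories. The answers can differ, because one failed criterion settles the first question while the second may remain open.

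Example: a six-hour headache is recorded with nausea/vomiting absent and photophobia absent, and the other fields are blank. Criterion D fails whatever the blanks contain, so the headache cannot be a migraine. If the blanks keep the physician from separating tension-type from other, the day is missing under SAP 6.1 and becomes a migraine day under SAP 10.4.3. Neither section exempts it.

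At stake is the content of the one confirmatory outcome: days that fail the trial's own definition could be counted at baseline and in weeks 9 to 12. This is separate from whether scoring truly undetermined headaches as migraine is conservative. The point here is which headaches the rule catches.

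**Working it through.** **1. The plan's own figure.** Inputs from SAP 7: difference 1.27 days, SD 4.20, two-sided alpha 5%, power 80%. Normal approximation: n = 2 × (1.960 + 0.842)² × 4.20² / 1.27² ≈ 172 per group. The exact t-test gives 173 (power 80.1%), as stated. This figure does not depend on the replacement rule; it supplies the scale for step 4.

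**2. Can an incomplete record already decide migraine yes/no?** Take the eight items behind B to D: B as one item, four C items, and nausea/vomiting, photophobia and phonophobia. Each is yes, no or missing.
- Incomplete patterns: 3⁸ − 2⁸ = 6561 − 256 = 6305.
- Patterns in which no criterion has failed: B 2 of 3; C 72 of 81 (it fails once three or more items are no); D 22 of 27 (it fails if nausea/vomiting is no and photophobia or phonophobia is no). 2 × 72 × 22 = 3168.
- Migraine excluded: 6561 − 3168 = 3393, less 201 complete patterns = **3192**.
- Migraine established: 1 × 33 × 11 = 363, less 55 complete patterns = **308**.
- Migraine open: 3168 − 363 = **2805**.

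Check: 3192 + 308 + 2805 = 6305. The 308 score as migraine either way. A yes/no trigger would replace only the 2805 open patterns. These are counts of logical patterns, not frequencies of days or patients. They show only that being incomplete for classification is not the same as migraine being undetermined.

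**3. Possible number of days.** The documents give no rate, so these are assumptions: 2 to 6 non-migraine headache days per 28 days, of which 5% to 30% are partly documented but already exclude migraine. Low end: 2 × 0.05 = 0.1. High end: 6 × 0.30 = 1.8 false migraine days per patient per 28 days. Days that also carry a migraine attack are unaffected.

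**4. Effect on the primary comparison** (t-test, 173 per group, SE = 4.20 × √(2/173) = 0.452).

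*Equal in both arms.* The mean difference is unchanged. If the false days add independent variation with SD s, the SD becomes √(4.20² + s²): s = 0.5 gives 4.23 and power 79.5%; s = 2.0 gives 4.65 and power 71.6%.

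*Unequal in weeks 9 to 12.* The net gap shifts the difference one for one:

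| Assumed net gap (days) | Type I error | Power for 1.27, gap against the app | Power for 1.27, gap favouring the app |
|---|---|---|---|
| 0.1 | 5.6% | 73.4% | 85.7% |
| 0.25 | 8.6% | 61.5% | 91.9% |
| 0.5 | 19.7% | 39.8% | 97.4% |

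With 4 non-migraine headache days per patient, these gaps need the affected share to differ between arms by 0.1/4 = 2.5, 0.25/4 = 6.25 and 0.5/4 = 12.5 percentage points.

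**5. Could completeness differ by arm?** At baseline both arms use the control app (protocol 10.2). Afterwards only the intervention arm sees classification, analysis and reports (protocol 7.1); the control app gives no feedback (protocol 7.2). SAP 4 states a seven-day limit on entering or editing for the control app and states none for the full app. Completeness could therefore diverge after randomization, in either direction. Adjusting for baseline does not remove a gap that arises later.

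**The case against.** The strongest reply is that the SAP already means the sensible thing. SAP 6.1 introduces the diary data as what is needed to judge B to D, and those are the only criteria it lists, so the respective information may simply be the B to D information. *Other* is a residual category, and a physician reading the raw diary could place the example headache there. This reading is possible, but the text does not state it: all three categories, including *other*, are conditional on sufficient documentation, and SAP 10.4.3 names the three-way split as its trigger. So the stronger statement a reader might infer, that such headaches will be counted, is not supported. They can be counted.

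The affected set may also be small or empty. SAP 6.1 says that the diary records timing, pain characteristics and symptoms for each documented attack, and nothing says that partly blank entries occur. A day answered yes on the daily question with no attack entry has no field that excludes migraine, so the point does not reach it. This stands, and it is why no number of days can be claimed.

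The rule is the same in both arms and both phases, and the ANCOVA adjusts for baseline. It is correct that this shows no bias in itself. It does not guarantee equal completeness under two different apps.

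A reader might also infer that the comparison with the algorithm is blind exactly where it matters, because *other* (no migraine day) and insufficient (a migraine day) have only *unclassified* as counterpart. The SAP gives no mapping of categories, so it does not say that insufficient against unclassified would pass as agreement. The check may or may not catch these days.

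**Conclusion.** The point holds as a defect of wording in the confirmatory endpoint. The trigger in SAP 10.4.3, with the condition in SAP 6.1, is wider than the endpoint needs and, followed literally, can turn a headache that fails B, C or D into a migraine day.

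The documents do not show how many days are affected, nor that the treatment difference is biased. A reader might infer bias from the type I error figures, but those rest on an assumed gap between arms of 0.1 to 0.5 days, with the planning SD of 4.20 and an unadjusted t-test. With equal rates the mean difference is unbiased and the cost is noise. Percentage measures are diluted somewhat: 10 days falling to 7 is a 30% reduction, but with one false day in each window it is recorded as 3/11 = 27.3%. That touches only patients near the responder threshold, on an explorative outcome.

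The change is worth making because it is cheap, uses diary data already collected, and keeps the conservative scoring wherever migraine is truly undetermined.

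**What to change.** In SAP 6.1 and 10.4.3, tie the rule to the yes/no question:
- A headache is set to missing, and then scored as a migraine day, only if the undocumented fields could still make B, C and D all fulfilled.
- If B, C or D already fails on documented fields, the blinded physician classifies the headache as non-migraine, even when tension-type and other cannot be separated. B is judged with the treatment qualifier that SAP 6.1 attaches to it.
- State whether a blank symptom field counts as absent or as unknown. Without this the first two sentences cannot be applied consistently.
- For the discrepancy check, compare physician and algorithm on migraine versus not migraine, and also re-evaluate every headache that the physician marks as insufficient.

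The physician keeps the final decision and the validated algorithm's output is unchanged. The cost is a few sentences, one derivation step on existing diary fields, and physician time for re-evaluating the insufficient entries. No new data are needed. The downside is slightly lower absolute migraine-day counts in both arms.
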